##### Cannabis Use

Cannabis use will be assessed by 4 items from the National Drug and Alcohol Strategy Household Survey (NDSHS) [62]. Items will assess whether participants have ever tried cannabis, their frequency of use in the past 6 months, and proportion of their friends and acquaintances who use cannabis. Emerging symptoms of cannabis use disorder will be screened by a 17-item DSM-5 symptom checklist, which assesses the absence or presence of symptoms in the past 12 months [60].

##### Other Substance Use

A total of 6 items from the NDSHS [62], allowing for comparison with a large representative group of Australians, will ask participants whether they have ever tried amphetamines, ecstasy, hallucinogens, sedatives, inhalants, or any other substance and their frequency of use in the last 6 months (on a 5-point scale ranging from “none” to “more than five times”). Questions will be presented alongside a table with alternative names for drugs. Cigarette and electronic cigarette use will be measured by 7 questions modified from Barrington-Trimis et al [63]. Questions assess whether participants have ever tried cigarettes or electronic cigarettes, their frequency of use in the past 6 months and 30 days, and the average quantity of cigarettes smoked per day in the past 30 days.

##### Mental Health Measures

Psychological distress in the past month will be assessed by the Kessler 6 scale [64] and the Distress Questionnaire-5 [60]. Depressive and anxiety symptoms during the past 2 weeks will be measured by the Patient Health Questionnaire-9 modified for adolescents [65] and the 7-item Generalized Anxiety Disorder scale, respectively [66]. The 3-item Mini Social Phobia Inventory [67] will screen for social phobia, whereas the Community Assessment of Psychic Experiences Positive Scale-15 [68] will measure psychotic-like experiences during the past 3 months. A total of 3 dichotomous questions drawn from the Youth Risk Behavior Surveillance System [69] and 1 question from the Patient Health Questionnaire-9 [65] will assess suicidal ideation in the past 12 months, including thoughts of and plans to attempt suicide.

##### Resource Utilization

Participants’ will be consented for access to Medicare Benefits Schedule and Pharmaceutical Benefits Scheme data providing detailed information on the number and cost of contacts with health care professionals and prescription medications reimbursed through these commonwealth-funded plans. These data will be obtained from the Department of Human Services for up to a 4.5-year period from the date of extraction. A retrospective 12-month questionnaire will also be used to capture resource use outside of Medicare Benefits Schedule and Pharmaceutical Benefits Scheme data, in addition to capturing some overlapping data for those participants who may not agree to this data access. The resource use questionnaire was adapted from the Client Services Receipt Inventory [70] and will assess the frequency of contact with health care professionals, other service utilization (eg, ambulance, self-help materials), overnight medical admissions, use of prescription medications, time off paid and unpaid work, support payments, and living arrangements.

##### Health-Related Quality of Life

Health outcomes will be assessed by the Child Heath Utility-9D [71], a pediatric health-related quality of life measure providing utility values for economic evaluations, which has been adapted for Australians aged 18 to 29 years [72].

#### Secondary Measures

##### Social Networks

All participants completing Web versions of the survey will also complete a social networks survey at each time point consisting of questions adapted from O'Malley et al [73] and Lau-Barraco et al [74]. Participants will be asked to nominate up to 6 people with whom they spent most of their free time with in the past 12 months. For each identified person, participants will be asked to report on this person’s demographics, relationships, frequency and mode of contact, perceived mental health symptoms, perceived alcohol consumption, whether they are considered a drinking associate, and relationship closeness. The relationships and closeness between pairs of nominated individuals will also be rated. Although these questions were not included in the original phase of the study, a subsample of participants were asked to nominate their 6 closest friends in their year at school to provide information on their social networks in the original CSC study.

##### Other Measures

Other secondary measures that will be administered include the following: (1) Bandura’s Resistive Self-Regulatory Efficacy Scale [75,76] will examine perceived self-efficacy to resist peer pressure to engage in high-risk activities; (2) the 8-item Frost Multidimensional Perfectionism Scale-Brief to measure perfectionism across 2 dimensions (striving and evaluative concerns) [77]; (3) the 11-item Emotion Regulation Questionnaire to assess individual differences in the use of 2 emotional regulation strategies (reappraisal and suppression) [78]; and (4) the Strengths and Difficulties Questionnaire 18+ to assess both internalizing and externalizing symptoms of participants [79].

### Statistical Analysis

Intention-to-treat analyses will be carried out for all primary and secondary outcomes in the trial, including all participants in the groups they were initially randomized to. Multilevel mixed-effects regression models will be used to assess these outcomes. Where appropriate, generalized mixed-effects models will be applied, for example, using logistic regression for dichotomous outcomes.

Multilevel models are able to account for the clustered design of the trial by taking into account the expected correlations between the multiple observations of each participant and between participants in the same school [80]. Multilevel models will include random intercepts for schools and random intercepts and slopes for time for individuals. The best fitting random effects structure for each model will be determined using likelihood ratio tests and model fit statistics such as the Akaike information criterion.

Models will include dummy-coded intervention terms that compare each intervention with the reference control group and time terms reflecting the survey occasion, along with covariates such as gender to adjust for possible confounding. The effects of greatest interest for assessing the effectiveness of the interventions are intervention × time terms that provide baseline-adjusted estimates of how each intervention group has changed relative to control. Interpretable measures of effect size such as odds ratios and standardized mean differences will be calculated for all effects as well their accompanying CIs.

Given that some outcome data are expected to be missing due to loss to follow-up, the analysis must also account for missing data. As mixed-effects models employ maximum likelihood estimation, they produce unbiased estimates when missing data can be assumed to be either missing completely at random or missing at random [81] and are considered to be superior to other strategies for dealing with missing data [82].

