### Study Design

This trial is registered with the Australian and New Zealand Clinical Trials Registry: 12613000723785. A total of 88 schools from the Australian states of New South Wales, Western Australia, and Queensland were recruited to the CSC trial in 2014. A total of 17 schools withdrew after randomization (primarily due to time constraints). The final cohort at baseline consisted of 6386 year 8 students from 71 schools (mean age 13.5 years [SD 0.6], 54.84% [3502/6386] female, 81.24% [5188/6386] born in Australia). Participating schools were randomized to 1 of 4 conditions: (1) Control (health education as usual), (2) *Climate Substance Use* (universal substance use prevention), (3) *Climate Mental Health* (universal mental health prevention), or (4) *CSC* (universal substance use and mental health prevention). Blocked randomization was used, allocating schools to the 4 conditions in equal ratios in blocks of 4. The CONSORT diagram (see Multimedia Appendix 1) summarizes participant flow and retention rates through the study for each condition. Comprehensive information about the intervention content, delivery, and study design of the original CSC study has been published in the original CSC study protocol [33]. The completed CSC study assessments and timeline for extended follow-up assessments can be seen in Multimedia Appendix 2.

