### Sample Size Calculations

Participants for this study come from 6386 students from 71 schools recruited to the original CSC study. Power calculations for the original trial were based on methods developed to detect intervention by time interactions in longitudinal cluster RCTs [52] and ensured adequate power to detect clinically significant differences across groups both in the total sample *and* in each of the 3 states of Australia where recruitment took place. These calculations accounted for 10% dropout at the school level and indicated that 2800 students recruited from 28 schools in each state (for a total of 8400 students) would achieve 80% power to detect a between-group mean difference of 0.15 (at the *P*<.05 level) with 7 measurement occasions. In our original study, we achieved a total sample size of 6386 students. Although this is not sufficient to do analyses at the state level, the total sample size is more than sufficient and far surpasses the 2800 required to detect the expected differences across the whole sample. As initiation and frequency of substance use as well as levels of depression and anxiety increase over the transition to early adulthood [9], larger effect sizes are expected over the longer-term follow-up. Thus, even allowing conservatively for dropout rates of >35%, the proposed follow-up study is adequately powered for the expected size of effect for *Climate Substance Use* (*d*=0.15), *Climate Mental Health* (*d*=0.15), and the *CSC* intervention (*d*=0.2). Power calculations based on the obtained sample, where there were at least 16 schools, and an average of at least 80 students per school in each intervention group show that the power to detect an effect size of *d*=0.15 at the final long-term follow-up would be >90%.

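### The stated mixed model has no school-level random effect for time, so the intervention × time tests are anti-conservative for any outcome on which schools differ in change

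*Protocol article*

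**What the plan says.** All references are to the protocol article.

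- **Unit of randomisation** (Study Design): blocked randomisation, "allocating schools to the 4 conditions in equal ratios in blocks of 4".
- **Deciding effects** (Statistical Analysis): "The effects of greatest interest for assessing the effectiveness of the interventions are intervention × time terms".
- **Random effects** (Statistical Analysis): "Multilevel models will include random intercepts for schools and random intercepts and slopes for time for individuals". Time slopes are given to individuals and not to schools.
- **Selection rule** (next sentence of the same section): "The best fitting random effects structure for each model will be determined using likelihood ratio tests and model fit statistics". AIC is the example given of a fit statistic. No candidate structures are listed, and neither a school slope nor a school-by-wave term is named or required.
- **Purpose claimed**: the same section presents multilevel models as the way to account for correlation between students of one school.
- **Scope**: the models cover all primary and secondary outcomes, with logistic versions for dichotomous ones.

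**The concern.** In a school-randomised trial, the error term for a treatment contrast has to contain the variation between schools in the quantity being compared. Here that quantity is change over time. A school random intercept shifts all waves of a school equally. It therefore drops out of change, exactly in a balanced linear model and approximately in a logistic one. With time slopes only at student level, the model assumes that two schools in the same arm have the same expected change and treats students as independent units for the deciding test.

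Where that assumption fails, standard errors are too small and the type I error exceeds 5%. The article itself gives reasons why schools might differ in change. Teachers deliver the classroom activities. Queensland students leave school a year earlier and are surveyed in a different calendar window, so whole schools share timing. The consequence would be false claims of lasting benefit, or of superiority of the combined programme over its components.

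**Working it through.** **Inputs**

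- Schools and students per arm (Sample Size Calculations): "where there were at least 16 schools, and an average of at least 80 students per school in each intervention group". So k = 16 and m = 80 before attrition.
- Attrition (same section): dropout above 35% is allowed for. 80 × 0.65 = 52 students per school.
- Significance level: 0.05 (same section), taken as two-sided; the article does not say.
- ρ, the share of between-student variance in change that lies between schools: not given. Assumed values are 0, 0.005, 0.01 and 0.02.

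**The plan's own figure.** The article gives no type I error for this model. Its nearest figure is power above 90% for d = 0.15 at the final follow-up. With 16 × 80 = 1280 students per arm and a single time point, power is 96.7% at ICC 0, 89.5% at 0.005 and 81.0% at 0.01. On change scores with an assumed within-student correlation of 0.7, it is 95.6% at 0.01. The claim can therefore be neither confirmed nor refuted, and no ICC for change can be recovered from it.

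**Step 1: stated structure, analytic.** The true variance of the contrast exceeds the model's by the design effect DE = 1 + (m − 1)ρ. The type I error of a nominal 5% test is 2 × [1 − Φ(1.96/√DE)].

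| ρ | DE = 1 + 51ρ | √DE | 1.96/√DE | Type I error |
|---|---|---|---|---|
| 0 | 1.000 | 1.00 | 1.96 | 5.0% |
| 0.005 | 1.255 | 1.12 | 1.75 | 8.0% |
| 0.01 | 1.510 | 1.23 | 1.60 | 11.1% |
| 0.02 | 2.020 | 1.42 | 1.38 | 16.8% |

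At ρ = 0.01 the true standard error is thus 1.23 times the reported one.

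**Step 2: check by mixed-model simulation.** Four arms, 16 schools per arm, 52 students per school, 8 assumed occasions, linear time, assumed variances, no intervention effect, 1000 runs per ρ (Monte Carlo standard error about 0.7 to 1.2 points).

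| ρ | Stated structure | With school slope | After LRT selection, school slope a candidate | LRT picks school slope |
|---|---|---|---|---|
| 0 | 5.3% | 4.9% | 5.3% | 3% |
| 0.005 | 8.8% | 5.4% | 7.9% | 21% |
| 0.01 | 11.8% | 4.5% | 6.1% | 58% |
| 0.02 | 16.3% | 5.5% | 5.6% | 96% |

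**Step 3: selection again, on change scores.** Same numbers of schools and students, 200,000 draws, with three selection rules (AIC, mixture LRT, one-df chi-square LRT). The ranges run across the rules.

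| ρ | School term dropped | Overall type I error after selection |
|---|---|---|
| 0.005 | 56-75% | 6.1-6.8% |
| 0.01 | 20-37% | 6.0-6.7% |
| 0.02 | 1-4% | 5.6-5.7% |

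When the term is always kept and 60 school-based degrees of freedom are used (64 schools − 4 arms), the error is 5.0% at ρ = 0.01. With a normal critical value it is about 5.5%.

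Steps 2 and 3 together give about 6-8% at 0.005, 6-7% at 0.01 and under 6% at 0.02, provided that a school slope is among the candidates.

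**The case against.** The strongest reply is that the stated structure is only a starting point. The next sentence lets the data choose the random effects for each model, and an analyst might well offer a school slope. If so, selection works best where the problem is largest: at ρ = 0.02 the slope is nearly always found and the error is under 6%. This stands, and the 8%, 11% and 17% must not be read as the error after such selection. But the article neither lists a school slope as a candidate nor requires one, and where ρ is small the selection usually misses it.

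A second reply is that a condensed article leaves model details to an analysis plan. That holds for the degrees-of-freedom method and for convergence fallbacks, whose absence is not criticised here. It does not hold for the random-effects structure, which the article states.

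A reader might also infer more than the text supports:

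- **That every primary and secondary outcome is tested at more than 5%.** No ICC for change is given. At ρ = 0 the stated test is valid, ρ may differ by outcome, and the arithmetic covers continuous outcomes only.
- **That the inflation should be worked out at 90 students per school (6386/71 = 89.9).** This ignores the attrition that the article expects; 52 is the fairer basis.
- **That selection could drop the school intercept and so do further harm.** The article says that intercept will be included. Because it cancels from change, dropping it would in any case hardly affect this test.

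**Conclusion.** Wrong as written; should be fixed. The stated structure leaves school-level variance in change out of the deciding standard error of a school-randomised trial. For any outcome with such variance, the type I error exceeds 5%: about 8%, 11% and 17% at an assumed ICC for change of 0.005, 0.01 and 0.02 with 52 students per school. The selection rule, if it considers a school slope, brings this down to between just under 6% and 8%; if it does not, it gives no protection. The mechanism follows from the text. The size rests on the assumed ICC range, the 35% attrition, balanced linear models and a two-sided 5% level. The documents do not show that the trial's tests will in fact reject too often, because the ICC may be zero and the candidate structures are not listed.

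**What to change.** In Statistical Analysis, or in the analysis plan:

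1. State that every model keeps a school random intercept and a school-level random effect for time, whatever the likelihood ratio test or AIC shows. Use a random slope if time is continuous, or a school-by-wave effect if wave is categorical.
2. Limit data-driven selection to the student-level covariance.
3. Base degrees of freedom for the intervention × time terms on schools (for example Satterthwaite, Kenward-Roger or between-within).

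It would also be prudent to name a fallback for non-convergence, such as school-level summaries of change or cluster-robust standard errors with a small-sample correction.

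The cost is a change of wording, somewhat wider confidence intervals and some convergence work. No data collection changes.

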Epidemiological studies show that between 40% [6] and 50% [7] of the population in Western countries will suffer from a depressive, anxiety, or substance use disorder during their lifetime. Furthermore, depression, anxiety, and substance use disorders typically emerge before the age of 25 years [8]. From the ages of 13 to 24 years, there is an increased susceptibility for the development of depression, anxiety, and substance use disorders. Longitudinal life course studies show that transitions from childhood to adolescence and from adolescence to young adulthood are marked by significant increases in anxiety disorders, depression, and substance use disorders [9]. In addition, even small elevations in mental health symptoms in adolescence increase the likelihood of developing a full-blown mental disorder later in life [10]. Substance use during adolescence is also a significant global problem, resulting in a number of adverse outcomes including violence, accidental injury, self-harm, suicide, and an increased risk of developing mental illness [11]. Although the majority of adolescents will not meet criteria for a full-blown substance use disorder [12], a substantial portion will use alcohol at harmful levels [13]. Data from nationally representative surveys consistently show rates of substance use (namely alcohol use) increase steeply between the ages of 13 and 18 years [14-16]. In the general population, approximately 25% of people with a substance use, anxiety, or mood disorder will experience comorbidity with another class of these disorders in any 12-month period [17]. Of particular concern, individuals with comorbid disorders are harder to treat, suffer a more chronic illness course, and experience poorer outcomes later in life than those with no disorder or single disorders [18,19].

To halt the escalation and associated burden of disease, prevention efforts need to be commenced before the onset and acceleration of substance use, depressive, and anxiety symptoms into well-established patterns and disorders. Adolescence is a key time to do this. School-based programs have been shown to reduce both substance use and depression and anxiety symptoms [20-22]. However, to date, prevention programs tend to target single disorders in isolation, ignoring the comorbidity and common risk factor shared by substance use and mental disorders [23,24]. Until recently, there were no prevention models targeting depression, anxiety, and substance use simultaneously.

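### With occasion-coded time, the intervention × time effect subtracts the baseline instead of adjusting for it: a modest efficiency loss for continuous outcomes, possibly a large one for substance use that is rare at age 13

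*Protocol article*

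**What the plan says.** Under Statistical Analysis: "Models will include dummy-coded intervention terms that compare each intervention with the reference control group and time terms reflecting the survey occasion". The effects of greatest interest are the "intervention × time terms that provide baseline-adjusted estimates of how each intervention group has changed relative to control". Dichotomous outcomes get a logistic mixed model. The random part is described as follows: "Multilevel models will include random intercepts for schools and random intercepts and slopes for time for individuals", with the final structure chosen by model fit.

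Baseline is therefore one of the outcome occasions, and the arm difference there is estimated freely. It is neither a covariate nor a mean shared by the arms. The text does not settle whether time is categorical or linear.

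Sample Size Calculations states that "the power to detect an effect size of *d*=0.15 at the final long-term follow-up would be >90" per cent. The Background says that "rates of substance use (namely alcohol use) increase steeply between the ages of 13 and 18 years".

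**The concern.** Schools were randomised, so apart from post-randomisation losses the expected baseline difference between arms is zero. Estimating it freely and subtracting it with a coefficient of 1 adds its sampling error to the contrast. Regression adjustment uses a coefficient estimated from the data, and over the seven years from about age 13.5 that coefficient is probably well below 1.

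The problem is sharpest on the log-odds scale. When few students use a substance at baseline, the baseline log odds are imprecise and the interaction inherits that imprecision. A real, sustained effect on alcohol or cannabis use could then be reported as null largely because use was rare at 13.

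**Working it through.** **Inputs from the article (Sample Size Calculations).** Groups have "where there were at least 16 schools" and "an average of at least 80 students per school in each intervention group", so k=16, M=80 and 1,280 students per arm. d=0.15; 5% level, taken as two-sided. Dropout of 35% leaves m=80×0.65=52 per school, or 832 per arm.

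**Assumed, because not stated.** ICC, baseline-to-final correlation ρ within participants, stability *a* of the school effect over time (*a*=1 is the plain school intercept in the plan), and prevalences.

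**The plan's own figure.** The >90% cannot be traced to one formula. At 1,280 per arm, an unclustered comparison of means gives 96.7%, a change score gives 89.4% at ρ=0.3 and 96.7% at ρ=0.5, and a linear slope gives 91.7% or more. The original 80% for 2,800 students (700 per arm) is matched both by an unclustered comparison and by a change score at ρ=0.5 (80.1% each).

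**Formulas, two occasions.** With residual variances w0 and w1 and school variance s²:

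- A = (w0/M + s²)/k
- B = [w1(1−ρ²)/m + w1ρ²/M + s²]/k
- C = [ρ√(w0·w1)/M + a·s²]/k
- Free baseline: V = 2(A + B − 2C)
- Baseline shared, or as participant and school-mean covariate: V = 2(B − C²/A)

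The difference is 2(A−C)²/A. It is never negative and is zero only when the regression coefficient C/A equals 1.

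**Continuous outcomes** (SD 1, w0=w1=1−ICC, s²=ICC, normal test). Example with ICC 0.01, ρ=0.3, a=1: A=0.001398, B=0.001777, C=0.000857. Free V=0.00292, SE 0.0541, power 79%. Adjusted V=0.00250, SE 0.0500, power 85%.

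Power, free / adjusted:

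| ICC | a | ρ=0.3 | ρ=0.5 |
|---|---|---|---|
| 0.01 | 1 | 79 / 85 | 90 / 92 |
| 0.03 | 1 | 80 / 83 | 90 / 92 |
| 0.05 | 1 | 81 / 83 | 91 / 92 |
| 0.01 | 0.8 | 73 / 81 | 83 / 88 |
| 0.01 | 0.5 | 64 / 76 | 73 / 82 |
| 0.05 | 0.8 | 54 / 60 | 60 / 65 |
| 0.05 | 0.5 | 35 / 44 | 38 / 47 |

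With a stable school effect the loss is about 1-6 points here, and 9 at ρ=0.1 with ICC 0.01. With drift (a=0.5-0.8, ρ=0.1-0.5) it is about 5-15. With no clustering at all it runs from 17 points (ρ=0.1) to 5 (ρ=0.5). A t test with 30 df changes the clustered losses by about half a point at most.

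Over ten assumed occasions with random intercepts and slopes and a stable school intercept (ICC 0.01 and 0.03), the loss is 0.2-5.6 points with categorical time and 0-1.2 with linear time.

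**Dichotomous outcomes** (delta method; w=1/[p(1−p)]; s²=[ICC/(1−ICC)]·π²/3; a=1; ρ=0.15; final prevalence 50%; log odds ratio 0.15·π/√3=0.272; t test, 30 df). Example with baseline prevalence 2%, ICC 0.03: w0=51.02, w1=4, s²=0.1018, so A=0.04622, B=0.01113, C=0.00803. Free V=0.0826, SE 0.287, power 15%. Adjusted V=0.0195, SE 0.140, power 47%.

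| Baseline prevalence | Free | Adjusted, ICC 0.01 | ICC 0.03 | ICC 0.05 |
|---|---|---|---|---|
| 2% | 15% | 64% | 47% | 38% |
| 5% | 27% | 65% | 51% | 45% |
| 10% | 40% | 67% | 56% | 52% |
| 20% | 53% | 68% | 62% | 59% |
| 30% | 58% | 69% | 64% | 62% |

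If final prevalence is 90% instead, the loss is 5-25 points over the same baseline range (clustering ignored).

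**The case against.** **The estimator is valid and the choice is defensible.** Both approaches are unbiased when arms are equal at baseline. Of 88 schools, 17 withdrew after randomisation, so equal baseline means among the remaining 71 are not assured, and a free baseline contrast guards against that. This stands: the point is efficiency, not bias or contradiction. It does not defeat the covariate version, which conditions on whatever imbalance is observed.

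**Subtraction also helps.** It removes stable school variance. At ICC 0.03, ρ=0.3 and 35% dropout, the free-baseline contrast has 80% power against 49% for a comparison of final values alone. This is why the loss is small under the school intercept as written. How stable school effects remain once participants have left school is uncertain; hence the drift rows.

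**Time coding.** A reader might infer that every age-20 estimate is affected however time is coded. The text does not support that. Individual random slopes suggest continuous time, where the continuous-outcome loss almost vanishes. Against this, the time terms are said to reflect the survey occasion and power is quoted for the final follow-up, so an occasion-specific contrast is a natural reading too.

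**Assumed prevalences.** The article says only that use rises steeply, and does not say which dichotomous variables will carry the primary conclusion. The dichotomous losses shrink markedly at 20-30% baseline prevalence.

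**Conclusion.** The point holds as a conditional efficiency weakness that the sponsor should correct. With occasion-coded time, the named effect of interest carries baseline sampling error that data already in hand could largely remove.

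For continuous outcomes the loss is modest under the model as written, larger if school effects drift, and negligible if time is linear. A flat loss of 5-17 points might be inferred, but that range needs two occasions, 35% dropout, zero ICC and ρ of 0.1-0.5; it is not a property of the plan. Nor should any loss be deducted from the stated >90%: the original power calculation was itself made for an intervention-by-time effect, and the basis of the later figure cannot be identified.

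The weight falls on dichotomous alcohol and cannabis outcomes that are rare at 13. At assumed baseline prevalences of 2-10%, the loss is about 12-49 points with ICC 0.01-0.05. These figures rest on assumed prevalences, ρ=0.15, a stable school effect and a delta-method approximation to the planned mixed logistic model.

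**What to change.** For every outcome with the same measure at baseline, and at minimum for dichotomous alcohol and cannabis outcomes, model the post-baseline occasions with the participant's own baseline value and the school-mean baseline as covariates. Report the adjusted difference or odds ratio for each planned comparison at years 5, 6 and 7. State how time is coded. Keep the intervention × time model as a sensitivity analysis.

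The cost is one changed model specification and its wording; no new data or participants are needed. The downside is small: participants without a baseline value must be imputed or dropped. The alternative of keeping baseline as an outcome with one mean shared by all arms avoids that, but assumes equal arms at baseline, which is less secure after the 17 school withdrawals.
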